## Abstract

**Background:**

Traditionally standard treatment for patients with early stage endometrial cancer (EC) is total abdominal hysterectomy and bilateral salpingo oophorectomy (TAH+BSO) with or without lymph node dissection through a vertical midline incision. While TAH is an accepted effective treatment, it is highly invasive, visibly scarring and associated with morbidity. An alternative treatment is the same operation by laparoscopy. Though in several studies total laparoscopic hysterectomy (TLH+ BSO) seems a safe and feasible alternative approach in early stage endometrial cancer patients, there are no randomized data available yet. Furthermore, a randomized controlled trial with surgeons trained in laparoscopy is warranted in order to implement this technique in a safe manner. The aim of this study is to compare the treatment related morbidity, cost-effectiveness and quality of life in early stage endometrial cancer patients treated by laparoscopy versus the standard open approach.

**Methods:**

A multi centre randomized clinical phase 3 trial, including 5 university hospitals and 15 regional hospitals in the Netherlands. Only gynecologists trained in performing a TLH are allowed to participate. Inclusion criteria: Patients with a clinical stage I endometrioid adenocarcinoma or complex atypical hyperplasia are randomized in a 2:1 allocation to receive TLH or TAH. The main outcome measure is the rate of major complications, as assessed by an independent clinical review board. In total, 275 patients are required to have 80% power at α-0.05 to detect a significant difference of 15% complication rate. Secondary outcome measures are 1) costs and cost-effectiveness, 2) minor complications, and 3) quality of life. All data from this multi center study are reported using case record forms. Data regarding quality of life, pain, body Image, sexuality and additional homecare are assessed with self reported questionnaires.

**Discussion:**

A randomized multi center study in early stage endometrial cancer patients with inclusion criteria for patients and surgeons is designed and ongoing. Results will be presented at the end of 2009.

**Trial Registration:**

*Dutch trial register number NTR821*.

## Background

Endometrial cancer is the third most common cancer in women in Western countries, accounting for 6–9% of their cancers, with a peak incidence at the age of 55–65 year. Endometrial cancer is a disease of the elderly and 90% of patients are over 50 years of age. The incidence increases in obese women and 70% of the patients have a high body mass index (BMI >25) and 50% have co-morbidity such as diabetes and cardiovascular disease. A total of 75% of the patients are diagnosed with stage I disease. Traditionally standard treatment for patients with early stage endometrial cancer (EC) is total abdominal hysterectomy and bilateral salpingo oophorectomy (TAH+BSO) with or without lymph node dissection through a vertical midline incision. While TAH is an accepted effective treatment, it is highly invasive, visibly scarring and associated with adverse events such as blood loss and wound problems [1,2]. Morbidity of laparotomy in case of endometrial cancer can be substantial due to frequent obesity and co-morbidity in this patient group and hospital stay is usually at least one week [1]. A good alternative approach for patients with early stage disease is by laparoscopy.

Laparoscopy in early stage endometrial cancer is a minimal invasive technique compared to the standard approach by laparotomy. In several retrospective and prospective studies it has been shown that the laparoscopic approach is an effective and safe alternative to the open procedure. Most of these studies show a significant reduction in treatment related morbidity, with shorter hospital stay, less pain and quicker return to activities in daily life with the laparoscopic approach compared to laparotomy [1-10]. The advantages of the laparoscopic approach seem to be even more pronounced in obese [2] and elderly patients [10,11] due to reduced complications and a shorter hospital stay. However, the only randomized controlled trial comparing the laparoscopic approach with the open approach was in benign disease [12]. This study is in a different group of patients (young, healthy) than the study population of the here proposed study i.e. elderly women with endometrial cancer. It is known that complications occur more frequently during the initial learning curve of this procedure and some authors suggest a quantity control (i.e. > 25 TLH procedures) for surgeons before participating in studies. [12]

Arguments often mentioned hampering the implementation of level three laparoscopic procedures are the high preoperative costs and the long learning curve. However, despite the fact that peroperative costs are higher for laparoscopy due to expensive disposables, it might be that the overall costs will be finely balanced between both procedures due to reduction of morbidity and shorter hospital stay [13,14].

Although randomized studies on this issue are not available yet, studies in which endometrial cancer patients are treated show similar rates and patterns of recurrence. Patients who underwent a TLH+BSO have similar recurrence rates when compared to TAH+BSO, as reported in a retrospective mono-centre study [3] and in two prospective mono-center studies [6,15]. In view of these data we proposed a randomized controlled clinical trial in which total laparoscopic hysterectomy performed by trained surgeons is compared to total abdominal hysterectomy in patients with early stage endometrial cancer.

## Methods

### Aims&design

The aim of this study is to compare treatment related morbidity, cost-effectiveness and quality of life in early stage endometrial cancer treated by laparoscopy (TLH+BSO) or laparotomy (TAH+BSO).

We hypothesize that laparoscopy will result in less treatment-related morbidity in patients treated for early stage endometrial cancer in a cost-effective manner. The study will also provide insight on whether the laparoscopic approach will improve quality of life as compared to the standard abdominal approach. The proposed research concerns a multi-center prospective randomized clinical phase 3 trial (including at least 15 centers) comparing major complication rate in patients with early stage endometrial cancer, randomized to surgical treatment by laparotomy (TAH+BSO) or laparoscopy (TLH+BSO).

### Eligibility criteria

#### Inclusion criteria patients

Early stage endometrial cancer patients (endometrioid adenocarcinoma grade 1 or 2, clinically stage I disease, negative endocervical curettage), after signed written informed consent, age 18 years and older are eligible for this trial.

#### Exclusion criteria patients

Exclusion criteria: other histological types than endometrioid adenocarcinoma of the endometrium, clinically advanced disease (stage II to IV), uterine size larger than conform 10 weeks gestation and cardio pulmonary contra indications for laparoscopy.

### Patient recruitment and consent

Eligible patients are identified and counseled by the gynecological staff of participating hospitals. Before entry into the study the gynecologist explains to potential subjects the aims, methods, reasonably anticipated benefits and potential hazards of the study. Before study entry, on all patients an endocervical curettage is performed to make sure that the patient has clinical stage I disease and the cervix is not involved.

Subjects are informed that their participation is voluntary and that they may withdraw consent to participate at any time during the study. In every center an independent medical doctor is available for more detailed information both for patients and colleagues if required. After sufficient information, written informed consent has to be obtained. The consent form must be signed before performance of any study-related activity. Patients who decide not to participate in this study are treated according to standard treatment protocol (TAH+BSO). Patients undergo routine physical examination and blood tests prior to the operation in either treatment arm, which is part of the standard procedure before surgery.

### Randomization and collection of baseline data

The patients to be enrolled in this trial are allocated to the TAH or TLH arm by computer randomization. For randomization, blocks of x patients are created such that balance is enforced within each block, stratified per center. Randomization is 2:1 for intervention to provide more exposure to data on the new laparoscopic procedure. We also expect a better enrolment in the study if the patients have a twofold chance of being allocated to the laparoscopic group as the reduced morbidity seems to be substantial. At study entry, all woman have baseline demographic, past gynecologic and medical history recorded in a case record form (CRF). After randomization, but prior to surgical treatment, patients are asked to fill in a questionnaire, consisting items regarding: quality of life (SF-36, EQ-5D), pain (VAS), Body Image Scale (BIS), sexuality (SAQ) and a questionnaire on additional homecare. (see figure 1)

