### Follow-up

Outcomes are assessed pre-operatively, after 6 weeks, and after 3 and 6 months, being the moments of routine control assessments and be registered on a case record form (CRF) by the treating physician and checked by the research nurse (status review) (see figure 1). Costs are assessed by a cost assessment (CRF and patient questionnaire). The doctor registers costs on a CRF related to the use of operation materials (disposables), operating time, duration of hospital stay, and treatment of complications.

All adverse events are followed until they have abated, or until a stable situation has been reached.

Data regarding quality of life (SF-36, EQ-5D), pain (VAS), Body Image Scale (BIS), sexuality (SAQ) and additional homecare are assessed with help of self reported questionnaires 6 weeks, 3 and 6 months after the operation (see figure 1).

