### Study parameters/endpoints

#### Main study parameter/endpoint

Our primary endpoint is: major complication rate. The following major complications are registered: injuries of bowel, bladder, ureter, vessel, nerves; thrombo-embolic events such as DVT (Deep Venous Thrombosis) or pulmonary embolism; haematoma requiring surgical intervention; hemorrhage requiring transfusion and/or surgical intervention; wound dehiscence requiring surgical intervention or re-admission; wound infections including vaginal vault abscess, requiring surgical intervention and/or prolonged hospital stay and/or readmission and/or treatment; other major complications.

The severity of a complication is scored according to the Common Terminology Criteria CTCAE version 3.0. An independent Complication Review Board of three experienced clinicians is asked to assess and judge all recorded complications and differentiate between major and minor complications, blinded to treatment arm. This Complication Review Board decides also if the complication is related to the operative procedure, as expressed by the following statements: not related, unlikely related, possibly related, probably related or definitely related. *http://ctep.cancer.gov/protocolDevelopment/electronic_applications/docs/newadverse_2006.pdf*

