#### Secondary study parameters/endpoints

1) Cost effectiveness

2) Minor complications. Outcomes are assessed by analyzing the CRF. An independent clinical review panel differentiates between major and minor complications, blinded for treatment arm and also assess whether the complication is related to the operative procedure.

3) Quality of life (SF-36 and EUROQOL), sexual functioning (Sexual Activity Questionnaire), Body Image Scale (BIS) and pain (Visual Analogue Scale).

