### Statistical analysis

#### Sample size

Sample size estimates are based on the ability of the study to detect changes in the primary outcome measure, rate of major complications. In this study, we choose for an unbalanced randomization (2(TLH+BSO):1(TAH+BSO)). Group sample sizes of 161 and 81 achieve 80% power to detect a difference of 0.15 between the null hypothesis that the major complication rate is 25% in both the TAH + BSO and the TLH + BSO group and the alternative hypothesis that we will observe a complication rate of 25% in the TAH + BSO group and of 10% in the TLH + BSO group, using a two-sided Chi-square test with continuity correction and with a significance level of 0.05. Assuming a drop-out percentage of 10%, 275 patients are needed.

The assumptions regarding these expected complication rates are based on the complication rates reported in (retrospective) studies comparing TAH with TLH. In addition, this is supported by the major complication rate of 9.26% that we found during the learning curve in our pilot study. The drop-out percentage of 10% can be expected when patients, after randomization, are unhappy with their allocated treatment and choose to end their participation in the study or due to incomplete or lost data.

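### Baseline self-reported scores are taken after randomization, when patients very probably know their arm, so baseline-referenced comparisons of the secondary patient-reported outcomes could be biased

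*Protocol article*

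**What the plan says.** The section of the protocol article on randomization and collection of baseline data fixes the order of events: "After randomization, but prior to surgical treatment, patients are asked to fill in a questionnaire". The battery covers "quality of life (SF-36, EQ-5D), pain (VAS), Body Image Scale (BIS), sexuality (SAQ) and a questionnaire on additional homecare". The same section has demographics and medical and gynecologic history recorded at study entry; only the self-reported scores are tied to a time after randomization.

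The same instruments "are assessed with help of self reported questionnaires 6 weeks, 3 and 6 months after the operation" (Follow-up). Quality of life, sexual functioning, body image and pain together form the third secondary endpoint, and quality of life is one of the stated aims.

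Two statements bear on what patients know and prefer. The sample size section attributes part of the 10% drop-out to "patients, after randomization, are unhappy with their allocated treatment and choose to end their participation in the study". The randomization section justifies the 2:1 ratio partly by saying "We also expect a better enrolment in the study if the patients have a twofold chance of being allocated to the laparoscopic group". Blinding appears only for the review of complications, whose board is to "differentiate between major and minor complications, blinded to treatment arm".

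The section on descriptive statistics plans summaries per arm at each assessment, and analysis of variance and/or regression for continuous variables. It does not say how the baseline score enters those analyses.

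**The concern.** A baseline is a safe reference point or covariate because allocation cannot have influenced it. That guarantee is lost once a self-reported score is taken after the patient has learned her arm. Disappointment at drawing open surgery, or relief at drawing laparoscopy, can move answers on quality of life, pain and body image before any operation. The protocol itself expects a preference for laparoscopy and some dissatisfaction with the allocation, so such a reaction is foreseeable.

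If TAH patients score worse at baseline for this reason and the reaction fades by follow-up, they appear to recover more. Change from baseline then understates the benefit of TLH, and baseline adjustment does so to a smaller degree. At stake is the interpretation of the patient-reported secondary endpoint.

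A second, smaller worry is that patients who leave on learning their arm may never fill in the baseline form, so missing baselines may differ between arms.

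**Working it through.** **Step 1. Timing.** The randomization section is explicit that the questionnaire follows randomization and precedes surgery. No other section places it earlier. The Follow-up section says only that the first assessment is pre-operative, which fits either order. Figure 1, the assessment schedule, was not visible in the text available for review.

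**Step 2. Knowledge of the arm.** The article does not say when patients are told. It does expect some to leave after randomization because they dislike the allocated treatment, which presupposes that they know it. No blinding of patients is described. Knowledge at completion is therefore a strong inference, not a stated fact.

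**Step 3. Group sizes.** The stated evaluable sizes are 161 TLH and 81 TAH. They reproduce: with 25% against 10%, two-sided 0.05 and continuity correction, the power at these sizes is

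Φ[(0.15 − 0.0093 − 1.96 × 0.0487) / 0.0536] = Φ(0.846) = 80.1%.

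Here 0.0093 = ½(1/81 + 1/161), and 0.0487 and 0.0536 are the standard errors under the null and the alternative. The figure is not in question; only the group sizes are used below.

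**Step 4. Illustration of size.** The article gives neither the shift nor the correlation, so both are assumptions. Let d be the allocation-induced difference at baseline in SD units and ρ the correlation between baseline and follow-up. Assume equal SDs, no true difference at follow-up, and a reaction present only at baseline.

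- Base standard error: √(1/81 + 1/161) = 0.136 SD.
- Change score: bias of size d; standard error √(2(1 − ρ)) × 0.136.
- Baseline-adjusted comparison: bias of size ρd; standard error √(1 − ρ²) × 0.136.
- Two-sided rejection rate: 1 − Φ(1.96 − bias/SE) + Φ(−1.96 − bias/SE).

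For ρ = 0.5 and d = 0.2:

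- Change score: SE = 1 × 0.136, bias/SE = 1.47, rejection 31.2%.
- Baseline-adjusted: bias 0.10, SE = 0.866 × 0.136 = 0.118, bias/SE = 0.85, rejection 13.5%.

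| d (SD) | ρ | Change-score bias | Rejection | Adjusted bias | Rejection |
|---|---|---|---|---|---|
| 0.1 | 0.3 | 0.10 | 9.5% | 0.03 | 5.6% |
| 0.1 | 0.5 | 0.10 | 11.4% | 0.05 | 7.1% |
| 0.1 | 0.7 | 0.10 | 15.8% | 0.07 | 11.1% |
| 0.2 | 0.3 | 0.20 | 23.7% | 0.06 | 7.5% |
| 0.2 | 0.5 | 0.20 | 31.2% | 0.10 | 13.5% |
| 0.2 | 0.7 | 0.20 | 47.4% | 0.14 | 30.2% |

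**Step 5. Direction.** If TAH patients score worse at baseline, the bias runs against TLH. The excess rejections would then nearly all be spurious results favouring TAH. If TLH has a real benefit, the practical effect is that it is underestimated by the amount in the bias column.

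**Step 6. After reordering.** With the questionnaire completed before randomization, the expected allocation-induced difference is d = 0, so this bias is zero in both analyses. The sample size does not change.

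**The case against.** The strongest reply is that the article commits to no analysis that uses this baseline. It names neither a change score nor a baseline covariate, and a plain comparison of scores at 6 weeks, 3 months or 6 months escapes the problem entirely. How baseline is handled may properly be left to an analysis plan that is not shown. This stands, and it makes the bias conditional on the analysis chosen. It does not remove the point: the timing of the baseline is fixed in this document, and no later analysis can restore a pre-allocation measurement.

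A reader might infer that the documents show patients answering with knowledge of their arm. They do not: the time of disclosure is nowhere given. The inference is strong, but it remains an inference.

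A reader might also infer that loss of baseline forms differs by arm. The article gives a single 10% drop-out, not split by arm, which also covers incomplete or lost data. Differential loss is possible but not shown. Patients who end participation would also lack follow-up scores, so an earlier baseline would not recover their outcomes.

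Finally, the size rests on assumed inputs and on a reaction that is gone by follow-up. If it partly persists, the net distortion of the change score differs. That is fair, and the figures should be read only as an illustration.

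**Conclusion.** The point holds as a possible, conditional bias. The article places the baseline patient-reported scores after randomization, when patients very probably know their arm. Any change-from-baseline or baseline-adjusted comparison of quality of life, pain, body image or sexuality could therefore be distorted. For assumed shifts of 0.1 to 0.2 SD and a correlation of 0.5, the bias is 0.1 to 0.2 SD for change scores and half that for adjusted comparisons. Over correlations of 0.3 to 0.7, two-sided error ranges from 9.5% to 47.4% for change scores and from 5.6% to 30.2% with adjustment. Whether a shift occurs, how large it is and which way it runs are unknown.

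It would be tempting to conclude that the trial's main result is at risk. The documents do not support that: the primary endpoint is the major complication rate, judged by a board blinded to arm, and it has no questionnaire baseline. The point is worth correcting because the remedy is cheap, but it is confined to secondary outcomes.

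**What to change.** Reword the section on randomization and baseline data so that the questionnaire is offered after written informed consent and before randomization. Completion should be encouraged but not made a condition of entry. Excluding women who decline a battery that includes a sexuality questionnaire could cost enrolment in a trial whose primary endpoint is surgical complications.

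For patients already enrolled, record the questionnaire date relative to randomization. Base the main patient-reported comparison, or at least a sensitivity analysis, on post-operative scores without the post-randomization baseline. If that baseline is reported by arm, label it as post-randomization data.

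The costs are small. Randomization waits briefly for one questionnaire, and because the trial is under way it will hold two kinds of baseline that must be flagged. Leaving out the baseline costs some precision against adjustment: at an assumed correlation of 0.5, the standard error is 0.136 rather than 0.118 SD, so intervals are about 15% wider (0.136/0.118 = 1.15). Against change scores at that correlation nothing is lost, since both standard errors are 0.136 SD.

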**Figure 1 F1:**
[figure not shown]
**Assessment schedule**.

At local centers, data collection is the responsibility of the local participating gynecologist and research nurses. The data collected in this study are coded and processed with adequate precautions to ensure patient confidentiality.

### Interventions

In this trial, the standard surgical approach TAH +BSO (table 1) is compared to the investigative surgical procedure TLH+BSO (table 2).

**Table 1 T1:** Surgical treatment protocol for a TAH, total abdominal hysterectomy

Preoperatively thrombosis prophylaxis is given
Preoperative antibiotic is given at least 15 min before skin incision;

Positioning of the patient in lithotomy position.

Vertical midline incision

Abdominal washing for cytology

Bipolar coagulation or sealing of the round ligament, cutting with monopolar scissors. Opening of the peritoneum of the bladder and the pelvic sidewall.

Bipolar coagulation or sealing of the infundibulopelvic ligament, cutting with monopolar scissors

Preparation of the bladder off the vagina

Skeletting the uterine vessels, coagulation or sealing of the vessels, after identification of the ureter.

Coagulation or sealing and cutting of the sacrouterine ligaments.

Taking out the uterus. Closing of the vaginal cuff by abdominal stitching.

Mass closure of sheath, skin closure.

**Table 2 T2:** Surgical treatment protocol for a TLH, total laparoscopic hysterectomy

Preoperatively thrombosis prophylaxis is given
Preoperative antibiotic is given at least 15 min before skin incision;

Positioning of the patient in lithotomy position.

Insufflation of CO2 and placing of the troicarts (4).

Abdominal washing for cytology.

Bipolar coagulation or sealing of the round ligament, cutting with monopolar scissors. Opening of the peritoneum of the bladder and the pelvic sidewall.

Bipolar coagulation or sealing of the infundibulopelvic ligament, cutting with monopolar scissors.

Placing the vaginal tube (the Mc Cartney tube). Preparation of the bladder off the vagina.

Skeletting the uterine vessels, coagulation or sealing of the vessels, after identification of the ureter.

Coagulation or sealing and cutting of the sacrouterine ligaments.

Cutting the vaginal wall on the rim of the vaginal tube. Keeping the ureter in sight.

Taking out the uterus. Closing of the vaginal cuff by abdominal or vaginal stitching.

